### Mindfulness intervention

First, the ALCOMEDIIT module will offer an initiation to mindfulness meditation (MM), a so-called indirect strategy aimed at modifying unwanted automatic responses by strengthening self-control skills, especially by automating self-control processes as well as by facilitating a more efficient executive functioning ensuring cognitive and behavioral control mechanisms. Indeed, a possible tool to fight against impulsivity towards the desire to consume alcohol is MM [17]. MM is described as “the awareness that emerges from purposefully paying attention, in the present moment and without judgment, to the unfolding of experience from moment to moment” [18]. MM-based interventions have already proven to be effective in reducing a variety of substance uses, particularly in an adult population [19]. More specifically, the Mindfulness Based Relapse Prevention (MBRP) program has demonstrated its clinical value in terms of reducing the desire to use drugs and the risk of relapse in people who received inpatient or outpatient treatment in an addiction clinical center [20]. However, this type of program requiring an 8-week investment would be difficult to integrate into a prevention approach aimed at regulating alcohol consumption and binge drinking in the student population because of its cost in terms of time and the mobilization of healthcare personnel. To date, very few studies have examined the usefulness of a brief intervention based on MM principles as part of a prevention program for students who are not in the process of treatment. To our knowledge, only one exploratory study has attempted to evaluate the effectiveness of a mindfulness-based brief intervention for students with binge drinking [21]. This first study yielded promising results highlighting the effectiveness of MM in decreasing the frequency of BD use and reported negative consequences related to alcohol consumption as well as in increasing feelings of self-efficacy and mindfulness (i.e., the willingness to pay attention to and accept the experience of the present moment as it is). Nevertheless, these results need to be replicated given the relatively small sample size. In addition, this study has some limitations and questions that the ALCOMEDIIT prevention program will attempt to address. Indeed, the ALCOMEDIIT project is not limited to a 1-month follow-up but also includes an exploratory 6-month follow-up offering the possibility to test the potential beneficial effects of the prevention program over time. Apart from the 1- and 6-month follow-up sessions, information concerning alcohol consumption and daily practice of MM can be collected in an ecological way within a mobile application allowing to prevent possible mnemonic biases often generated by retrospective recall of memories at a distance from the event. The ALCOMEDIIT project also places the control group in a brief intervention condition by having all the participants benefit from a motivational interview, thus making it possible to determine the specific benefits linked to the MM intervention.

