#### Experimental group

Similar to the control group, participants will benefit from a motivational interview with the psychologist who welcomed them for inclusion. Yet, this motivational interview will be completed by two activities: mindfulness-based initiation and implementation intention exercises.

The mindfulness meditation session is structured in four steps. The session begins with the meditation called “grape exercise” associated with the “sound meditation.” In a second step, the principles of mindfulness meditation (conceptualization of MBM, autopilot and acceptance) are explained to the participants by the psychologist. The session continues with two exercises, the first named “Sitting Meditation Space on thoughts” and the second “SOBER Breathing Space in the face of 1 Challenge situation.” At the end of the session, an explanation on the memo sheet available on the mobile application is given to the participants so that they can continue their practice if a risky substance use situation arises.

The implementation intention session follows the MBM initiation. It focuses on the implementation of two behaviors, on the one hand, regular MBM-based training (II-1) and, on the other hand, the use of MBM in risky drinking situations (II-2). The two systematic phases related to an II process are specific to each of the two implementations (all details available on osf: https://osf.io/3n4c6/.

II-1 deals with the implementation of a daily and/or regular use of MBM. It focuses first on the identification by the participant of a situation, in terms of place, moment of day, and context, which represents an opportunity to reach the goal of practicing MBM on a regular basis, or an obstacle to reaching this goal (II-1a). Then, the participant is invited to identify a thought or behavior that is relevant, for him or her and in this situation that he or she has chosen, to seize this opportunity or overcome this obstacle (II-1b). On this basis, the participant is invited to explicitly formulate the link between these two elements in the linguistic format “If (II-1a), then (II-1b),” to copy it once, to repeat it quietly in his/her head 3 times while trying to represent the scene concretely. The participant must repeat the exercise a second time by proposing another “II-1a” and another “II-1b.”

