A second step will consist in conducting the main analyses. Recall that by “five dependent variables (DVs),” we mean here binge drinking score (BD), weekly alcohol consumption (WAC), craving, impulsivity, and readiness to change (RC). Prior to the main analyses, we will check whether there is a significant relationship between age and the baseline scores of any of the five DVs. We expect the age range to be rather small apart from potential serious outliers, in a sample that is not particularly large, and we do not expect age to play a noticeable role on most of the DVs, except for BD scores where it is suspected that binge drinking behaviors are most common in the younger population. For these reasons, we want to avoid adding age as a covariate unless the data show that we really have to. We will conduct five similar general linear analyses, with the following variables: dependent variable: evolution scores (T0 → T1) of one of the five DVs; factors: condition, sex, condition*sex; covariates: AUDIT score, baseline of the DV at hand. Covariate(s) that will be added if either they are significantly related to the baseline scores of the DV at hand, or the two groups were not matched at T0 with respect to them: age, trait anxiety level, depression level. We add as a covariate the baseline of the DV at hand because we expect that the higher level of self-consciousness brought by the very fact of taking part in this demanding study might trigger an effect of regression to the mean, by which people with a larger baseline score (and hence a larger margin for improvement) would show better results no matter in what condition they were placed.

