In the main analysis, the use of evolution scores as a DV has a number of consequences. First, the effect of condition as reported in the analysis can actually be interpreted as an interaction effect between condition and the within-subject time factor. Second, the condition factor will be dummy-coded (experimental = 1; control = 0) so that the intercept of the model corresponds to the average evolution in the control group, in other words the effect of motivational interviewing alone (plus the fact of having to report your data on a daily basis), while the condition effect will correspond to the added value of the mindfulness training. We will investigate the simple effects of condition and sex, should their interaction turn out to be significant. All these analyses will be repeated using the evolution scores T0 → T6 as well.

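### As the model is written, the intercept is not the control arm's mean change, and the condition contrast measures the combined module rather than mindfulness alone

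*Protocol article*

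**What the plan says.** All of the modelling text is in the Protocol article, Data management and analysis plan. The outcome is the change from T0 to T1 in each of five variables, repeated for T0 to T6. The terms are "factors: condition, sex, condition*sex; covariates: AUDIT score, baseline of the DV at hand". Age, trait anxiety and depression may be added. The section states neither centring of the covariates nor a contrast for sex.

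On coding, it says "the condition factor will be dummy-coded (experimental = 1; control = 0" in parentheses, "so that the intercept of the model corresponds to the average evolution in the control group". It then restates the intercept: "in other words the effect of motivational interviewing alone (plus the fact of having to report your data on a daily basis". Of the other coefficient it says "while the condition effect will correspond to the added value of the mindfulness training". Simple effects of condition and sex are to be examined only if their interaction is significant.

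On attribution, the Mindfulness intervention section says that giving everyone the interview has a consequence: "thus making it possible to determine the specific benefits linked to the MM intervention". The Experimental group section describes what that arm receives: "this motivational interview will be completed by two activities: mindfulness-based initiation and implementation intention exercises".

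**The concern.** The plan fixes in advance how its two main coefficients will be read, and neither reading follows from the model and design it describes.

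- **Intercept.** Dummy-coding one factor makes the intercept a group mean only if every other term is zero at its average. Uncentred covariates are not. A reader who takes the intercept as the interview-only result could report a rise in binge drinking where the control arm fell.
- **Condition.** The arms differ by two active components, but the result would be credited to one. This matters because the Dissemination policy section plans to discuss transfer of the programme with local prevention services.

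**Working it through.** The plan prints no value for either coefficient, so there is no figure to reproduce. Its sample-size and power figures play no part here.

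**Inputs from the Protocol article.** Mean decrease of 10% (control) and 20% (experimental), and within-subject SD of one quarter of baseline plus 0.5 (Power analysis). 1:1 allocation (Study design and setting). BD score above 1 and age 18 to 30 (Eligibility criteria).

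**Assumed, because the article does not give them.** Mean baseline BD score m = 20 (range 15 to 25), gamma shape 1.5, 60% women, and an AUDIT score correlated with baseline but with no effect of its own.

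**Step 1: intercept.** Write b for baseline.
- Expected change is -0.10b in control and -0.20b in the experimental arm.
- The model has one common baseline slope. With equal arms it is (-0.10 - 0.20)/2 = -0.15.
- In the control arm the fitted mean equals the observed mean: intercept - 0.15m = -0.10m. So the intercept is **+0.05m**, while the control mean change is **-0.10m**.

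| Mean baseline m | Control mean change | Intercept, uncentred |
|---|---|---|
| 15 | -1.5 | +0.75 |
| 20 | -2.0 | +1.0 |
| 25 | -2.5 | +1.25 |

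The signs are opposite for any positive m.

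**Step 2: check of the full model** (400,000 simulated participants, m = 20).

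| Coding | Intercept | Condition coefficient |
|---|---|---|
| Uncentred, sex treatment-coded | +1.01 | -2.02 |
| Uncentred, sex sum-coded | +1.02 | -2.03 |
| AUDIT and baseline centred, sex treatment-coded | -2.04 | -2.02 |
| AUDIT and baseline centred, sex sum-coded | -2.02 | -2.03 |

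The control arm's mean change was -2.01. Centring the covariates repairs the intercept; recoding sex alone does not. For a given coding of sex, centring leaves the condition coefficient unchanged, because condition does not interact with AUDIT or baseline.

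**Step 3: can a correct control mean be the interview effect?** Both arms receive the interview, so nothing in the trial shows change without it. The same section justifies the baseline covariate by expecting regression to the mean whatever the condition. The control mean change therefore mixes the interview, daily reporting and regression to the mean.

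**Step 4: what the condition contrast compares.** Experimental arm: interview, mindfulness session, implementation-intention session. Control arm: interview. The difference is the two-part module, and two arms cannot divide it between its parts.

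**Step 5: sex, a conditional point.** With condition*sex in the model and sex at R's default treatment coding, the condition coefficient is the effect in the reference sex. Its variance is about 4σ²/(N × share of that sex), against 4σ²/N without the interaction, so the SE ratio is 1/√share: 1/√0.35 = 1.69, 1/√0.50 = 1.41, 1/√0.65 = 1.24. If the true effect differed by sex (assumed 2.5 percentage points of baseline in men and 15 in women; overall difference -2.01), the coefficient would be -0.55 with men as reference, -1.77 with sum coding (unweighted average of the sexes), and -2.01 with sex centred at its mean.

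**The case against.** Contrasts and centring are ordinary detail of an analysis plan. The article points to a separate one that is not shown, so silence on centring does not prove that covariates enter uncentred. That is fair as far as silence goes. But the article is not silent on the intercept: it names dummy-coding of condition as what gives the intercept its meaning, and in the model it lists that is not sufficient. The correction is to a stated rule.

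The intercept is not the trial's test. This stands. A reader might infer that the primary comparison is biased or invalid; Step 2 shows that it is not.

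A reader might also infer that the primary test is a single-sex test with lower power. The documents do not support that. Coding is stated for condition only, and leaving simple effects until after a significant interaction suggests that an overall effect is intended. With effect-coded sex the problem disappears, so Step 5 is a condition to be settled and not a finding.

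A baseline of 0 is shown to be outside the population only for the BD score. No AUDIT minimum is stated, and the other four outcomes have their own ranges.

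On attribution, the abstract, the Study objectives and the Discussion all describe the combination, so the wording on mindfulness training may be shorthand. That softens the analysis section, but the claim in the Mindfulness intervention section about specific benefits goes beyond shorthand. Extra contact time is inherent in an add-on design and is not a fault here. The parenthesis on daily reporting shows some caution, but it leaves out regression to the mean.

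**Conclusion.** The point holds in this form. As written, the intercept does not have the meaning the plan gives it. For the BD score, under the plan's own 10% and 20% decreases, it is about +0.05 times the mean baseline instead of -0.10 times it, a reversal of sign. The reversal needs equal allocation, a common baseline slope and uncentred covariates. The values +1.0 and -2.0 also need the assumed mean of 20. No such figure is derived for the other four outcomes. If age is added as the plan allows, an uncentred intercept would also refer to age 0, outside the eligible 18 to 30.

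Separately, and whatever the coding, the control mean is not the effect of interviewing alone, and the condition contrast belongs to the combined module. The single-sex reading remains conditional on an unstated coding of sex.

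What changes is the reported control-arm result and the interpretation of both coefficients. The between-arm estimate and p-value do not depend on centring AUDIT and baseline.

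**What to change.** - Centre AUDIT, the baseline of each outcome and any added covariate, and centre or effect-code sex. Say which, since sum coding gives an unweighted average over the sexes and mean-centring a sample-weighted one. Alternatively, report adjusted mean change per arm and their difference averaged over sex, without interpreting the intercept.
- Keep the prespecified condition*sex term. Once sex is coded as above, there is no need to remove it.
- Describe the control-arm value as the mean change in the control arm, not as the effect of motivational interviewing.
- In Data management and analysis plan and in Mindfulness intervention, name the contrast as the added value of the combined mindfulness and implementation-intention module over the interview.
- If the separate analysis plan already fixes centring and the sex contrast, align the article's sentence with it.

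The cost is analysis-plan wording and a few lines of code. Data collection, sample size and participants are unaffected.

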### Study design and setting

All the study design and setting (see SPIRIT Checks in Additionnal File 1) has been elaborated by the trial steering committee (TSC) which is made up of the research team who authored this article, with the exception of Messrs [name] and [name], who were respectively responsible for the development and design of the ALCOODUC mobile app. The TSC, comprising nine people, is made up of academics specializing in prevention issues and field experts specializing in alcohol-related problems and/or the practice of mindfulness meditation. This steering committee met on a monthly basis during the protocol design phase and validated each stage of the protocol submission process, notably at the level of the national ethics committee (see the “Ethics approval and consent to participate” section for a brief description of the French system).

This is a randomized controlled study in parallel groups. It will compare the monthly BD score between the control group and the experimental group, and the allocation ratio is 1:1.

One hundred seventy volunteer participants from the University of Caen (France) will be included in this research protocol (see Fig. 1). During the initial visit, after presentation of the study and signature of the consent form presented by one of the two psychologists in charge of the interviews, all participants will complete various online questionnaires (estimated completion time 40 min; LimeSurvey) as well as a screening for neuropsychological impairments using the BEARNI tool (Brief Evaluation of Alcohol-Related Neuropsychological Impairments [33]; estimated completion time of 20 min). Eighty-five participants will benefit from the control condition (i.e., a motivational interview), and 85 other participants will benefit from the experimental condition (i.e., a motivational interview associated with a mindfulness meditation session and intention implementation; estimated duration 1 h).

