#### Motivation to use mindfulness meditation (RTC-Meditation)

In order to assess participants’ behavioral changes regarding the practice of mindfulness meditation, we will offer the RTC-Meditation questionnaire (based on the RTC-Alcohol) to all students included in the study.

Once the neuropsychological evaluation and all the questionnaires have been completed (estimated duration 50 min), on the basis of a random assignment (see randomization procedure with envelopes), the participant will be integrated into the control group or the experimental group. Regardless of the group, all participants will participate to a motivational interviewing session. Only the experimental group will participate in a mindfulness meditation session associated with an implementation intention session.

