#### Control group

Participants in the control group will receive no specific psycho-social intervention except that they will benefit from a motivational interview with the psychologist who welcomed them for inclusion.

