### Statistical considerations

#### Power analysis

At an alpha risk of .05, the number of 120 subjects in total is sufficient to obtain a power greater than .80. This estimate is derived from a 3000 iteration Monte Carlo simulation based on a baseline of real data collected in November 2021 (*N* = 1917) with a Gamma distribution. In this simulation are parameterized an average decrease of 10% of the BD score in control group and an average decrease of 20% for the experimental group with an intra-subject variability (SD) linearly depending on the individual baseline (estimated to be ¼ of the baseline value + 0.5).

Considering a potential attrition rate of approximately 30%, 170 subjects will be included in the study at T0.

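### The control arm's before-after change is labelled the effect of motivational interviewing, which a design giving the interview to both arms cannot identify

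*Protocol article*

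**What the plan says.** The section Data management and analysis plan models evolution scores for five dependent variables: binge drinking score, weekly alcohol consumption, craving, impulsivity and readiness to change. Condition is dummy-coded (experimental 1, control 0) "so that the intercept of the model corresponds to the average evolution in the control group". The sentence continues by giving that quantity a causal meaning: "in other words the effect of motivational interviewing alone (plus the fact of having to report your data on a daily basis"). The condition effect is read as what the mindfulness training adds. All analyses are then repeated for T0 to T6.

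Just before this, the same section justifies the baseline covariate. It expects that taking part in a demanding study may trigger regression to the mean, so that people with higher baselines "would show better results no matter in what condition they were placed".

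On the arms, Study design and setting describes two parallel groups in which "the allocation ratio is 1:1". The text that closes the list of measures says: "Regardless of the group, all participants will participate to a motivational interviewing session". The Control group section adds: "Participants in the control group will receive no specific psycho-social intervention except that they will benefit from a motivational interview".

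**The concern.** A before-after change in one arm is the sum of everything that happened to those participants over the interval. To attribute it to the interview, one needs a group that differs only in not having had the interview, and this trial has none. The label therefore gives a causal meaning to a number that is descriptive.

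What is at stake is what may be concluded from the control arm. The Background says that the interview's effectiveness is debated. If the label is carried into the results, a fall in the control arm would be presented as evidence on that debate, although a fall could occur with an interview that does nothing. The comparison between arms is not at stake.

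**Working it through.** The point turns on identification, and the plan gives no figure for the interview's effect to reproduce. I set out what each arm's change contains and then give an illustration of size.

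**Step 1. Components of change.** Assume that effects add and that randomisation makes the shared ones equal across arms. Write:

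- I = effect of the interview (both arms)
- R = effect of daily reporting in the app (both arms)
- P = effect of taking part (both arms; expected by the analysis plan)
- M = regression to the mean (both arms; expected by the analysis plan)
- T = any other change over time or in measurement (both arms)
- A = the added module, mindfulness with implementation intention (experimental arm only)

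Then:

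- control change = I + R + P + M + T
- experimental change = I + R + P + M + T + A
- difference = A

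The two arm means identify the shared sum and A. They do not split the sum. The plan's label sets the control change equal to I + R, which requires P + M + T = 0. The preceding paragraph of the same section expects P and M not to be zero.

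**Step 2. Other shared contributors that the document itself gives.**

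- Participants are selected on the outcome: the Eligibility criteria require a binge drinking score above 1.
- The Discussion presumes that volunteers are already motivated to reduce their drinking.
- Under Binge drinking practices, the episode count covers a year at T0 (divided by 2) and a month at T1 (multiplied by 6). The scaling agrees, since 12 × monthly count ÷ 2 = 6 × monthly count, but the recall window differs. Any resulting shift cancels between arms and does not cancel within the control arm.

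**Step 3. Does the baseline covariate help?** Take the case most favourable to the plan: covariates centred and sex coded so that the intercept equals the control arm's average change. The baseline slope then describes how change varies between participants with higher and lower scores. It does not remove the average shift of a group selected on that score, nor participation or time effects. These stay in the intercept.

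**Step 4. Extent.** Five dependent variables × two intervals (T0 to T1, T0 to T6) = 10 intercepts carry the label.

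**Step 5. Illustration of size (assumed inputs).** Set I, R, P and T to zero and leave only M. The document gives no score distribution for the trial sample, so I assume:

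- true scores Gamma with mean 15 and shape 1.5, hence variance 15² / 1.5 = 150
- normal measurement error, independent at the two visits, with variance 150 × (1 − r) / r for reliability r
- the same noisy score used for selection (above 1) and as baseline

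| r | Error variance | Mean baseline if selected | Mean change | Change |
|---|---|---|---|---|
| 0.9 | 16.7 | 16.54 | −0.45 | −2.7% |
| 0.6 | 100 | 19.41 | −2.51 | −12.9% |

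For comparison, the Power analysis assumes "an average decrease of 10% of the BD score in control group". Under these assumptions, a control decrease of about that size can arise when the interview has no effect.

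The illustration is rough. Normal error lets some simulated scores fall below zero. If the T0 score were taken independently of the screening score, part of the regression would occur before T0. It shows that the label can be materially wrong; it does not estimate by how much in this trial.

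**The case against.** The strongest reply is that nothing in the trial rests on this clause. It explains a coding choice. The objectives concern adding mindfulness and implementation intention to the interview, the Interventions section frames the trial as superiority of the experimental over the control condition, and the Mindfulness intervention section says that everyone receives the interview, "thus making it possible to determine the specific benefits linked to the MM intervention". The other half of the disputed sentence reads the randomised contrast as the effect of the added training. This stands, and it limits the point to one planned interpretation.

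A reader might infer more: that the trial will test the intercept and report the result as evidence that the interview works, or that prevention services will be told so. The document does not support either inference. It announces no hypothesis or test for the intercept, and the Dissemination policy speaks of the transferability of the whole programme.

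A second reply is that the authors qualify the label by mentioning daily reporting, and that they plainly know of regression to the mean. The qualification is real but incomplete: it admits one non-interview contributor and omits the ones expected in the paragraph before it.

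A third reply is that the separate analysis plan may settle how the intercept is reported. It may. The point concerns a sentence that is present in the article, not an omission.

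**Conclusion.** The interpretation is wrong as written. The control arm's average change is an uncontrolled before-after change, and the interview's effect is not identified at T1 or T6 for any of the five outcomes, whether or not baseline is adjusted for. This follows from the arm definitions alone; no numerical assumption is needed.

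The error has no computable size, because the data cannot apportion the control change. The range of −2.7% to −12.9% rests entirely on the assumed distribution and on reliabilities of 0.9 to 0.6. An upward trend over time could equally hide a benefit of the interview.

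It would be too strong to say that the trial fails in its purpose. The condition effect, the primary comparison and the stated objectives are untouched.

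**What to change.** In Data management and analysis plan, remove the clause that equates the intercept with the interview's effect. Suggested replacement: *the intercept describes the control group's average change over the interval, under the interview, self-monitoring in the app, and all other effects of time and of taking part; it will be reported descriptively with a confidence interval and is not an estimate of the interview's effect. Causal conclusions will be drawn only from the condition effect.* Apply the same wording to the T0 to T6 analyses.

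The cost is wording only: no change to data collection, sample size, model or power. The downside is that the control-arm change can no longer be presented as an interview effect.
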